#### Study procedures (Figure 1)

**Figure 1 F1:**
[figure not shown]
**Combined study flow-chart**.

##### Recruitment

Eligible subjects and their families will be approached by the research nurse and the local principal investigator (PI) and they will be provided with a verbal explanation of the study and written information sheets. Once they have been given sufficient time to consider their participation in the trial, the parents will be asked to provide written informed consent and children to provide evidence of their assent to the study procedures.

##### Baseline Assessment

Once consent has been obtained, baseline assessments will be undertaken within 3 months of recruitment. These will include measurement of height, weight, waist circumference (WC), arterial BP and assessment of pubertal stage. Blood samples will be taken for measurement of HbA1c, total cholesterol, triglycerides, HDL-cholesterol, LDL-cholesterol, lipoproteins, SDMA, creatinine, cystatin C, CVD markers (hsCRP and ADMA) and DNA extraction. All subjects will also have alanine aminotranferase (ALT) and urea and electrolytes (U&E) assessed locally and post-menarchal sexually active girls will have pregnancy tests. All subjects will be asked to attend designated centers for cIMT assessment and, where facilities allow, also FMD, EndoPAT and PWV. They will be asked to complete a simple quality of life questionnaire and a short questionnaire for Health Economic analysis. Anonymised digital copies of the most recent retinal photographs, performed as part of the routine annual screening, will be also collected for centralized assessments.

##### Randomization

Eligible subjects who have provided informed consent and have completed baseline assessments will be randomized by the PI using a secure internet-based service http://www.sealedenvelope.com. This provides randomization with minimization [77]. Subjects will be allocated to one of four treatment regimens after minimizing differences between arms on the following baseline characteristics: HbA1c (<7.5, 7.5-8.5, > 8.5%), log mean standardized ACR (>1.2 to <1.7, >1.7), gender, age (11-13, >13 years), duration of disease (<5 years, >5 years), total cholesterol (≥ 4.46 or < 4.46 mmol/l).

##### Initiation of therapy

Following confirmation of patients' eligibility for the trial they will be randomized, and intervention will commence. Subjects will be instructed by the research nurse/PI about the administration and the storage of the investigational medical products (IMPs). Furthermore, the patients and their parents will be informed about possible side effects related to the drug and will be instructed to report any adverse events during treatment. Contact during the first four weeks of treatment will be maintained weekly by the research nurse, through visits or by telephone at pre-arranged times.

##### Treatment period assessment

Subjects will be seen two weeks after commencing treatment for assessment of compliance, adverse events and adjustment of the dose of Quinapril/Placebo. Subjects will be seen again after one month, when toxicology tests will be also performed (ALT and U&E). Every three months subjects will undergo a routine clinical assessment with local measurement of HbA1c. Six-monthly assessment will include: three consecutive early morning urines for ACR, height, weight, waist circumference, pubertal stage, BP, smoking status, HbA1c, blood lipids and lipoproteins, plasma SDMA, creatinine, cystatin C and CVD biomarkers, toxicology (ALT, U&E) and pregnancy tests. Compliance will be assessed by return of study drugs and drug bottles with electronic track caps. Quality of life and health economics will be assessed annually with a questionnaire. At each annual visit, subjects will be asked whether they have undergone routine annual retinal screening and anonymised digital copies of retinal photographs will be collected for centralized assessment.

##### Final assessment

The final assessment after 3-4 years of the intervention will be identical to the initial assessment and will include measurement of cIMT and, where facilities allow, FMD, EndoPAT and PWV. Anonymised digital copies of the most recent retinal photographs, performed as part of routine screening, will be collected for centralized assessment.

##### Run-out assessments

At the end of the intervention period and following the final study assessment, all study drugs will be withdrawn and subjects will be followed for a 6-month run-out period. At the end of this period subjects will be asked to provide a final blood sample and three early morning urines for assessment of ACR and MA status and measurement of lipids, lipoproteins, CVD risk markers, SDMA, creatinine and cystatin C. These data will be used to inform physicians as to the need for re-starting IMP according to local prescribing guidelines in subjects aged 15-19 years.

##### Long-term follow-up

Consent is obtained in the initial consent procedures for possible long-term surveillance through postal questionnaires and possible recall 5 and 10 years after study initiation. In the UK registration with the Office for National Statistics (ONS) may also be sought.

#### Investigational Medical Products (IMPs)

The active drugs (Atorvastatin and Quinapril) will be manufactured by Pfizer, along with appropriate placebos with adherence to Good Manufacturing Practices. Atorvastatin will be provided in a single dose of 10 mg daily for oral administration with an identically labeled placebo (Study drug A). Quinapril will be available at 2 doses: 5 mg and 10 mg with appropriately matched placebo (Study drug Q). Subjects will be started on 5 mg and reviewed after two weeks; if there have been no adverse reactions in this time, the dose will be increased to 10 mg daily, otherwise it will maintained at 5 mg. Any subjects experiencing apparent side effects (postural hypotension or persistent cough) will have the option of changing to the lower dose at any point during the study.

Subjects will be instructed to take two tablets per day; Pharmacists will be instructed to dispense the blinded product according to the schedule and advised that dose of Study drug Q may need to be reduced. All drugs will be given orally as tablets. No subject will be exposed to more than 10 mg of Quinapril or 10 mg of Atorvastatin. Subjects will be treated with the IMPs for a minimum of three years and up to four years depending on age at recruitment.

Both ACEI and Statins are licensed for use in children and adolescents in the UK, Australia and Canada. However the product licenses are related to the treatment of hypertension in non-diabetic subjects and the treatment of hyperlipidaemia in subjects with familial hypercholesterolaemia. To facilitate the use of the drugs in children with T1D an appropriate Clinical Trial Authorization has been obtained from regulatory authorities in the UK, Canada and Australia.

The drugs and placebo will be delivered to Catalent Pharma Solutions, the contracted distribution company that will be responsible for packaging, labeling and distribution of the IMPs to the designated pharmacies at the study sites. Electronic pill bottle monitoring caps supplied by AARDEX (Zug, Switzerland) will be used. These track caps incorporate a micro-electronic circuit, which records each opening and closing in order to track compliance.

Central pharmacies will dispense the IMPs to the study subjects through the research nurses employed by the local PIs. The nurses will then instruct the patients about the proper storage and use of the drugs, including the return of all unused tablets. IMPs will be dispensed according to local requirements as stated in Standard Operating Procedures (SOPs) and taking account of local regulations.

Common adverse drug reactions have previously been reported for Atorvastatin [78] and Quinapril [79]. For the purposes of adverse event reporting during study visits, particular attention will be paid to possible hyperkalemia, persistent dry cough, hypotension, GFR decline, ALT levels for liver function and muscular pain/rhabdomyolysis. Both Quinapril and Atorvastatin are contra-indicated during pregnancy because of concern about teratogenecity and because they may interfere with early fetal growth and result in stillbirth. See additional file 2 for more information.

#### Blinding and Emergency unblinding

The subject, local investigator and all study and project management staff will be blinded as to treatment allocation. Subjects will be randomized using the web-based system and the Cambridge coordinating center will receive notification of randomization within 24 hours. The randomization website http://www.sealedenvelope.com provides a facility for emergency unblinding of drug allocation. Each PI will be provided with a password which will allow access to their patients' treatment allocation. All emergency unbinding will be at the discretion of the local investigator, when clinically indicated for the safety of the patient. Unblinding will also be possible through the pharmacy. Investigators should refer to SOPs for the unblinding procedure. All unblindings are automatically notified by email to the study-coordinating center in Cambridge to prevent abuse of the system and to ensure rapid notification to the data monitoring and ethics committee (DMEC) of potential serious adverse events (SAEs).

#### Compliance

Subject compliance will be assessed at each 3-monthly study visit, when all unused study drug will be returned and will be recorded in the CRFs by the research nurses. AARDEX electronic pill bottle track caps, which permit checks of the number of times the pill container has been opened between study visits [80,81], will also be used. The track cap data will be available locally through software provided by AARDEX and can be used by the study nurses to encourage compliance and where appropriate introduce interventions to improve compliance. We will also make regular contact with study subjects through newsletters identifying the value of continued involvement in the study protocol.

#### Withdrawal of study drugs

With exception of pregnancy, if it is deemed necessary to withdraw a patient from one of the study drugs this will not preclude their continuing participation in the study. Subjects withdrawn from either of the study IMPs will be encouraged to remain in the trial.

#### Rescue medications

Patients developing clinical hypertension will be treated at the discretion of the local investigator. Treatment is initially expected to be a diuretic, followed by the use of a calcium channel blockers (or similar agent). Very high cholesterol levels, perhaps related to familial hypercholesterolaemia rather than T1D will be identified at baseline as an exclusion criterion. However, if at any time during the intervention period LDL cholesterol levels are found to be above 4.6 mmol/l and/or triglyceride levels are above 9 mmol/l, the central laboratory will notify the site. A first attempt to reduce lipids levels will be made by improving the patient's glycaemic control and dietary intervention; a second lipid measurement will be performed within four weeks. If the second value is still above the threshold, the case will be notified to the DMEC for consideration of withdrawal from the study. If at any time during the study, the ACR is in the macroalbuminuric range (ACR>35 mg/mmol in males and >47 mg/mmol in females [13]), these cases will be notified to the DMEC for consideration of withdrawal from the study

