## 1. Randomised Controlled Clinical Trial (Study 1)

### Study Objectives

#### Primary

To determine whether intervention with ACEI, Statins, or combination therapy when compared with placebo, in a 2 × 2 factorial design over three to four years, will: 1) reduce albumin excretion as assessed by six monthly measurement of albumin/creatinine ratio (ACR) in 3 early morning urines; 2) reduce the incidence of MA (ACR >3.5 mg/mmol (males) or >4 mg/mmol (females) in 2 out of 3 urines) at the end of the study period; 3) reduce the incidence of MA during the six month run-out period following the completion of intervention phase.

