### Study endpoints

The primary endpoint is defined as the area under the curve over time of log ACR per year, with standardization for gender, age and duration of diabetes.

The secondary endpoints are: 1) changes in cIMT, FMD, EndoPAT and PWV between baseline and the end of intervention period; 2) changes in arterial BP, lipids and other lipoproteins, CVD risk markers (hsCRP and ADMA), assessed every 6 months during the intervention period; 3) changes in measures of GFR (plasma SDMA, creatinine and cystatin C) assessed every 6 months during the intervention period; 4) changes in retinopathy scores and retinal microvascular structure (arteriolar or venular dilation, vascular fractal dimension, branching and tortuosity), assessed annually; 5) changes in quality of life and health economics.

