### Methods/Design

#### Design of the RCT

The study is a multicenter randomized trial involving centers in the UK, Australia and Canada *(see additional file *1).

Subjects will be recruited from a pre-screened population of ~3,000 young people with T1D aged 11 to 16 years based on assessment of risk for future CVD and DN. Subjects deemed to be at high risk, based on their albumin excretion rate, will be randomized to a 2 × 2 factorial design contrasting the effects of ACEI, statins, or combination therapy to placebo over a three to four year treatment period. Minimization of variation between study arms in albumin excretion rate, gender, age, diabetes duration, HbA1c, total cholesterol and center location will be undertaken at randomization.

Analysis of the primary endpoint, change in albumin excretion, will be undertaken on an 'intention to treat' basis. Secondary analyses will be undertaken on the basis of 'as treated' allowing for variance in compliance and allowing for subjects who show substantial changes in HbA1c levels. Additional analyses will be undertaken to assess changes in the secondary objectives and to assess the overall effect of the intervention on quality of life and health economics.

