### Statistical analysis

Continuous measures will be compared between groups using analysis of covariance, whereas binary outcomes will be compared using logistic regression. These models will involve adjustment for the randomization stratifiers, and for pre-randomization baseline outcomes to improve precision. The primary endpoint was correlated with baseline standardized ACR in the ORPS cohort (r = 0.3) indicating potential improvement in precision of estimated treatment effects. An initial test will be undertaken for exclusion of the factorial interaction of ACEI with Statin, with subsequent estimation of the factorial main effects of ACEI and Statin and single-arm comparisons. Subgroup analyses, for gender and for baseline standardized ACR (using a median split), will be undertaken by adding an interaction between the subgroup variable and factorial main effects followed by estimation within subgroups. Sensitivity analyses, such as for compliance and for raised HbA1c, will involve analysis using the same methods but applied omitting the relevant subjects or the relevant observations within subjects. For the HbA1c sensitivity analysis exclusions will be defined as those observations following the initial occurrence of a change in HbA1c from baseline in excess of 1%. An analysis restricted to the initial two measurements (first year) where short-term compliance is considered greater, will be performed and contrasted with the later period using within-patient analysis. Missing data will be primarily handled by excluding missing observations from analysis and secondly by multiple imputations [91] considering a contrast of both optimistic and pessimistic scenarios for treatment effects. Analyses will be on the primary basis of intention to treat, with as treated and per protocol as secondary. All tests will be two-tailed, and 5% and 1% significance levels will be used for primary and secondary outcomes respectively.

Formal interim analyses have not been incorporated into the design and analysis of the trial because the 3 to 4 year period of follow-up per subject is long relative to the recruitment period, and an interim analysis would detect early improvements without informing maintenance of any effect. The independent DMEC will determine how regularly to review efficacy and safety regularly, based on progressively longer mean treatment durations.

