#### • Subject withdrawal

A subject may terminate participation in the study at any time without necessarily giving a reason and without any personal disadvantage. An investigator can stop the participation of a subject after consideration of the benefit/risk ratio. Possible reasons are: 1) serious adverse events; 2) non-compliance; 3) technical grounds (e.g. patient moves away); 4) early termination of the study at the request of the steering committee;

5) pregnancy. The reasons for withdrawal will be clearly documented in the CRF. For subjects who have withdrawn from the study for any of the reasons identified above, permission will be sought to use their data in an 'intention to treat' analysis and for further analyses of long-term outcome data. If they consent to further communication, long-term data collection relating to outcomes will be undertaken.

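### Referral for withdrawal from the study on high ACR or lipids, and stopping for non-compliance, permit loss of scheduled urines; the exposure is small and falls on late microalbuminuria, not the primary AUC

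*Protocol article*

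**What the plan says.** All references are to the protocol article.

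- **Rescue medications.** An ACR above 35 mg/mmol (males) or 47 mg/mmol (females) at any time leads to referral: "these cases will be notified to the DMEC for consideration of withdrawal from the study". LDL above 4.6 mmol/l or triglycerides above 9 mmol/l, if confirmed on repeat, lead to the same place: "If the second value is still above the threshold, the case will be notified to the DMEC for consideration of withdrawal from the study".
- **Withdrawal of study drugs.** Apart from pregnancy, stopping a drug does not end participation: "Subjects withdrawn from either of the study IMPs will be encouraged to remain in the trial".
- **Subject withdrawal.** An investigator may stop a subject's participation after weighing benefit and risk. "Possible reasons are: 1) serious adverse events; 2) non-compliance" opens the list. The section then says that permission will be sought to use withdrawn subjects' data in the intention-to-treat analysis, and that long-term outcomes will be collected from those who agree to further contact.
- **Design of the RCT.** "Analysis of the primary endpoint, change in albumin excretion, will be undertaken on an 'intention to treat' basis".
- **Study endpoints.** The primary endpoint is "defined as the area under the curve over time of log ACR per year", standardised for gender, age and duration.
- **Study Objectives, Primary.** The second objective is microalbuminuria (MA) at the end of the study. The third is to "reduce the incidence of MA during the six month run-out period following the completion of intervention phase".
- **Statistical analysis.** "Missing data will be primarily handled by excluding missing observations from analysis and secondly by multiple imputations". The imputation is to contrast optimistic and pessimistic scenarios.

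**The concern.** The protocol separates leaving a drug from leaving the trial, then does not keep to that distinction. ACR is the variable behind the primary endpoint and all three primary objectives. A rule that can end follow-up because ACR is very high can remove the later urines of the subjects with the worst outcomes, and such subjects should be more frequent without effective treatment. The lipid trigger may also act unevenly, because one factor of the design is a statin. Stopping participation for non-compliance works against intention to treat and is not needed, since the Statistical analysis section already plans as-treated, per-protocol and compliance sensitivity analyses.

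The AUC per year can be computed from the visits a subject has. End-of-study and run-out MA each depend on urines at one late time point, so they are the urine outcomes most exposed.

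**Working it through.** **1. Do the mitigations close the gap?** Permission to use withdrawn subjects' data covers urines already in hand. Long-term collection depends on consent and does not name the six-monthly, final or run-out urines. Multiple imputation with two scenarios addresses informative loss but comes second; leaving out missing observations is the primary handling. The gap that remains is urines never collected after withdrawal.

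**2. How often would the ACR trigger fire on the protocol's own distribution?** The sample size section gives standardised log10 ACR a mean of 0.28 and an SD of 0.38 (single value) or 0.28 (AUC, mean of 3.5 observations). Taking predicted ACR as 1.0 mg/mmol (assumed), for a single occasion:

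- Males: z = (log10 35 − 0.28)/0.38 = (1.544 − 0.28)/0.38 = 3.33, probability 0.0004.
- Females: z = (log10 47 − 0.28)/0.38 = (1.672 − 0.28)/0.38 = 3.66, probability 0.0001.

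**3. Variance components (compound symmetry assumed).** b + w = 0.38² = 0.1444 and b + w/3.5 = 0.28² = 0.0784. So w = 0.0660/(1 − 1/3.5) = 0.0924 and b = 0.0520.

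**4. Simulation.** One million subjects per arm, seven six-monthly visits and one run-out visit.

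- Treatment effect: log10(0.75) = −0.125 on treatment, fully reversed at run-out (assumed).
- Progressors (assumed): 0%, 4% or 10% in both arms, rising linearly by 1.4 log10 to the last visit. The 4% borrows the ORPS cohort figure for clinical proteinuria, which is not a 3-4 year rate; 10% is an upper case.
- Withdrawal: at the first visit above 35/47, for every crossing. This is an upper bound, because the DMEC only considers withdrawal.
- MA: a value above 3.5/4 mg/mmol, approximating two of three urines.

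Each arrow runs from all urines kept to urines after withdrawal missing. For MA, anyone who crossed is left out. Differences are control minus treated, in percentage points.

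| Progressors | Crossing, control v treated | AUC reduction | End-of-study MA difference | Run-out MA difference |
|---|---|---|---|---|
| 0% | 0.2% v 0.05% | 25.0% → 25.0% | 8.4 → 8.4 | 0 → −0.1 |
| 4% | 3.0% v 2.3% | 25.0% → 24.9% | 8.1 → 7.8 | 0 → −0.5 |
| 10% | 7.3% v 5.8% | 25.0% → 24.5% | 7.6 → 6.9 | 0 → −1.2 |

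The end-of-study shifts are 8.1 − 7.8 = 0.3 and 7.6 − 6.9 = 0.7 points. If subjects who first cross at the last visit still contribute that urine, the differences become 7.7 and 6.8. At run-out the true difference is zero, so the shift is a small spurious one against treatment.

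**5. A further assumption that enlarges the effect.** Suppose treatment also halves progression. With 4% / 10% progressors in control:

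- AUC reduction: 27.7% → 27.4% / 31.6% → 30.8%.
- End-of-study MA difference (subjects first crossing at the last visit keep that urine): 9.9 → 8.9 / 12.0 → 9.8.
- Run-out MA difference (anyone who crossed left out): 1.6 → 0.2 / 3.9 → 0.7.
- Counting withdrawn subjects as MA restores 9.9 / 12.0 and 1.6 / 3.9.

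Nothing in the protocol supports the halving.

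**6. A different model.** Random slopes with an assumed SD of 0 to 0.2 log10 per year replace progressors, with eight values and sex-averaged thresholds. At the largest SD the AUC reduction moves by about 0.6 points (24.9% → 24.4% as rounded) and the end-of-study MA difference from 5.1 to 4.0. The run-out shift runs from under 0.1 to 1.7 points against treatment. With no drift, nothing material moves.

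The protocol gives no rates for lipid referral or non-compliance stops, so neither was modelled.

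**The case against.** The two sections do not contradict each other: one concerns stopping a drug, the other a discretionary referral to an independent committee. That is right, and the point is one of poor fit. A reader might infer that subjects crossing the threshold are withdrawn automatically, or that their earlier data are dropped and intention to treat is broken. The text supports neither. Withdrawal is only to be considered, missing observations rather than subjects are excluded, and permission to use withdrawn subjects' data is sought.

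Much of the remainder could be left to the analysis plan. Subjects withdrawn for high ACR have an observed high value, so counting them as MA, or imputing from earlier values, recovers nearly all of the contrast. The protocol already makes continuous ACR the main indicator of MA because binary MA has little power. This stands, and it limits the severity. It does not help subjects lost through the lipid or non-compliance routes, whose MA status would be unknown, and no analysis plan can recover urines that were never collected.

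The article condenses a fuller protocol that may say what follows a DMEC withdrawal. That is possible, but the rule as printed names the study, not the drug. Recruiting 500 to analyse 400 protects power, not against outcome-related loss.

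**Conclusion.** The point holds as a minor one. The protocol permits withdrawal from the study for reasons tied to the outcome, and its mitigations do not secure the scheduled urines. The primary AUC is essentially unaffected. ACR-triggered withdrawals could bias late MA slightly towards no effect: close to zero on the protocol's own distribution, and about 0.3 to 0.7 points at end of study and 0.5 to 1.2 points at run-out with 4% to 10% assumed progressors and every crossing withdrawn. The random-slope model reaches 1.1 (5.1 − 4.0) and 1.7 points at its most extreme.

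A reader might infer from the larger figures that the run-out contrast would be largely erased. That rests on the added assumption that treatment halves progression. The bias from ACR-triggered withdrawal also works against treatment, so it would not manufacture a benefit. No size or direction is claimed for the lipid and non-compliance routes.

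**What to change.** - In Rescue medications, replace withdrawal from the study with stopping or changing study drug plus rescue treatment, as the DMEC and clinicians decide.
- In Subject withdrawal, make non-compliance a reason to stop study drug only.
- State that the six-monthly, final and run-out urines continue for all randomised subjects unless consent is withdrawn.

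How MA is classified when urines are still missing can stay with the analysis plan.

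The cost is a few sentences and a small follow-up burden. In the scenarios without halving, the ACR trigger concerns about 500 × (3.0% + 2.3%)/2 ≈ 13 to 500 × (7.3% + 5.8%)/2 ≈ 33 of 500 subjects, whose urines are already scheduled. One real change is that the DMEC's option becomes stopping drug rather than ending follow-up.
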